#### Data on exposure

Data on the running performed is collected using the smart-phone application. The smart-phone application is provided to the participant for free and synchronizes with the participants own smart-phone GPS, to collect the data on the running performed. A main feature of the smart-phone application is the live audio-feedback, provided to the participant regarding running pace. If a participant deviates from the scheduled running pace, by going too fast or too slow, the smart-phone application will provide an audio-feedback, until the participant is within the scheduled running pace.

#### Data on outcome

Outcome data is collected weekly using the Oslo Sports Trauma Research Center Questionnaire [25]. If full participation is not possible due to a perceived physical problem, the participant is contacted by telephone. If a participant reports an injury, an appointment for physical examination is made. Certified physiotherapists (the diagnostic team) perform the clinical examinations, using a previously employed standardized examination procedure [10]. Examinations are performed in the respective physiotherapeutic clinics, in which members of the diagnostic team are employed. After an examination, the physiotherapist reports data on diagnosis to the research group.

#### Baseline measurements

Participants complete the baseline measurements through the online training diary. The baseline measurements are divided into four parts which are administered consecutively.is self-reported and covers personal information, demographics, medical history, information on running experience and the social security number. The self-reported height and weight will be used to calculate BMI (weight (kg)/height^2^ (m^2^)).covers current symptoms of overuse injury, using a modified version of the Oslo Sports Trauma Research Center questionnaire (OSTRC) developed by Clarsen et al. [25], to establish a baseline measurement of overuse symptoms.covers the baseline assessment of general physical activity during daily life. The Short Questionnaire to Assess Health-enhancing physical activity (SQUASH) is a tool, which assess habitual activity level during an ordinary week. Questions are pre-structured in four categories and information on days per week, average time and effort is collected. Time to complete the SQUASH questionnaire has been estimated to be 3 – 5 min [28].and final part of the baseline measurement, is a field-based self-administered physical performance test (PPT). The participants are required to download the Help2Run smart-phone application, to complete the self-administered physical performance test. Through the smart-phone application the participants select 1 out of 3 possible running tests: 6 min running test, Coopers 12 min running test or 5 km running test. When the preferred test is completed, the test results are used to prescribe the intensity of running for each of the participants.

### Training variables

Four variables are used to design the running schedules for both intervention groups; frequency of running, progression in running, running volume and running intensity.

#### Running frequency

Running frequency is defined as the frequency at which participation in a series of stimuli per unit of time takes place [29]. Running frequency is quantified with each week as the time unit. The running schedule presents the running frequency, as the number of running session scheduled per week.

#### Running progression

Running progression is defined as the percentage increase in training load per unit of time [29]. The training load is quantified in kilometers with each week as the time unit. The running schedule presents the running progression as the percentage increase in kilometers between 2 weeks and as the percentage increase in kilometers between 2 and 4 week cycles.

#### Running volume

Running volume is defined as the total quantity of running [29] and is quantified in kilometers, combined with an indication of the time scale used. The running schedule presents the running volume as kilometers per session (km/session) and kilometers per week (km/week).

#### Running intensity

Running intensity is defined as the qualitative component of work performed in a given time [29]. The individual quantification of running intensity is divided into 3 intensities: easy pace ≈ 50–80%VO2max, moderate pace ≈ 81–87%VO2max and hard pace ≈ 88–100%VO2max [30]. The individual paces are presented as the minutes per kilometer (min/km) equal to the estimated VO2max, which are based on the results from the self-administered physical performance test, using the $$ {\overset{.}{V}}_{O_2} $$ (VDOT) values presented by Daniels et al. [31, 32]. The running schedule presents the running intensity as kilometers per week per specific pace (km/week/pace).

### Intervention

The training variables of interest are running intensity and running volume. Two running schedules have been designed, each with a specific focus on increasing either running intensity or running volume (Tables 1, 2 and 3). The training variables *running frequency* and *running progression* follow a similar fixed pattern in both training schedules throughout the 24-week follow-up. The 24 week running period consists of an 8 week preconditioning period and a 16 week intervention training period. The running frequency is 3 sessions per week for all weeks. Participants were advised to complete the weekly running sessions on the scheduled days (Tuesday – Thursday – Sunday), or preferably allow 1 day of recovery between running sessions. The overall progression in running follows a 4-week cycle. The 4-week cycle consist of a progression of 23 % in running (volume or intensity) the first week, a second and third adaptation week with 0 % progression and a fourth regression week with 10 % regression in running (Fig. 2).

**Table 1 Tab1:** The content of the running schedule during the 8-week preconditioning period

Preconditioning period							
Training variables	Intensity	Volume	Frequency			Progression	
Week	km/week/pace	km/week	km session 1	km session 2	km session 3	prog/week	prog/cycle
1	15 easy	15	5	5	5	NA	NA
2	15 easy	15	5	5	5	0 %	
3	15 easy	15	5	5	5	0 %	
4	13,5 easy	13,5	3,5	5	5	−10 %	
5	13,5 easy/3 moderate	16,5	5	5	6,5 (3moderate)	23 %	10 %
6	13,5 easy/3 moderate	16,5	5	5	6,5 (3moderate)	0 %	
7	13,5 easy/3 moderate	16,5	5	5	6,5 (3moderate)	0 %	
8	12 easy/3 moderate	15	5	5 (3 moderate)	5 inc. PPT	−10 %	

The content is displayed in relation to the four training variables: intensity, volume, frequency and progression and for each of the 8 weeks. The kilometers to be completed in each running session are outlined in the collums of session 1–3. All kilometers are run at an intensity equal to easy pace, except if moderate or hard is specified (easy pace ≈ 50-80 %VO2max, moderate pace ≈ 81-87%VO2max and hard pace ≈ 88–100 %VO2max). The volume outlined in the parenthesis will then be completed in the specified pace. The progression is in total weekly volume. PPT is the abbreviation used for Physical Performance test

**Table 2 Tab2:** The content of Schedule Intensity during the intervention training period

Intervention training period-schedule intensity							
Training variables	Intensity	Volume	Frequency			Progression	
week	km/week/pace	km/week	km session 1	km session 2	km session 3	prog/week	prog/cycle
1	15,5 easy/3 hard	18,5	5	7,5	6 (3 hard)	23 %	NA
2	15,5 easy/3 hard	18,5	5	6 (3 hard)	7,5	0 %	
3	15,5 easy/3 hard	18,5	5	7,5	6 (3 hard)	0 %	
4	13,8 easy/2,7 hard	18,5	5	6 (2,7 hard)	7,5	−10 %	
5	15,2 easy/3,3 hard	18,5	5	7,5	6 (3,3 hard)	23 %	9,50 %
6	15,2 easy/3,3 hard	18,5	5	6 (3,3 hard)	7,5	0 %	
7	15,2 easy/3,3 hard	18,5	5	7,5	6 (3,3 hard)	0 %	
8	15,6 easy/2,9 hard	18,5	5	6 (2,9 hard)	7,5 inc. PPT	−10 %	
9	15 easy/3,5 hard	18,5	5	7,5	6 (3,5 hard)	23 %	6 %
10	15 easy/3,5 hard	18,5	5	6 (3,5 hard)	7,5	0 %	
11	15 easy/3,5 hard	18,5	5	7,5	6 (3,5 hard)	0 %	
12	15,4 easy/3,1 hard	18,5	5	6 (3,1 hard)	7,5	−10 %	
13	14,7 easy/3,8 hard	18,5	5	7,5	6 (3,8 hard)	23 %	9 %
14	14,7 easy/3,8 hard	18,5	5	6 (3,8 hard)	7,5	0 %	
15	14,7 easy/3,8 hard	18,5	5	7,5	6 (3,8 hard)	0 %	
16	15,1 easy/3,4 hard	18,5	5	6 (3,4 hard)	7,5 inc. PPT	−10 %	

The content is displayed in relation to the four training variables: intensity, volume, frequency and progression and for each of the 16 weeks. The kilometers to be completed in each running session are outlined in the collums of session 1 – 3. All kilometers are run at an intensity equal to easy pace, except if moderate or hard is specified (easy pace ≈ 50–80%VO2max, moderate pace ≈ 81–87%VO2max and hard pace ≈ 88–100%VO2max). The volume outlined in the parenthesis will then be completed in the specified pace. The progression is in total weekly volume at a hard pace. PPT is the abbreviation used for Physical Performance test

**Table 3 Tab3:** The content of Schedule Volume during the intervention training period

Intervention training period-schedule volume							
Training variables	Intensity	Volume	Frequency			Progression	
week	km/week/pace	km/week	km session 1	km session 2	km session 3	prog/week	prog/cycle
1	15,5 easy/3 moderate	18,5	5	5	8,5 (3 moderate)	23 %	11,50 %
2	15,5 easy/3 moderate	18,5	5	8,5 (3 moderate)	5	0 %	
3	15,5 easy/3 moderate	18,5	5	5	8,5 (3 moderate)	0 %	
4	13,5 easy/3 moderate	16,5	5	6,5 (3 moderate)	5	−10 %	
5	17 easy/3 moderate	20	5	6	9 (3 moderate)	23 %	8,50 %
6	17 easy/3 moderate	20	5	9 (3 moderate)	6	0 %	
7	17 easy/3 moderate	20	5	6	9 (3 moderate)	0 %	
8	15 easy/3 moderate	18	5	83 (3 moderate)	5 inc. PPT	−10 %	
9	19 easy/3 moderate	22	5	7	10 (3 moderate)	23 %	10 %
10	19 easy/3 moderate	22	5	10 (3 moderate)	7	0 %	
11	19 easy/3 moderate	22	5	7	10 (3 moderate)	0 %	
12	17 easy/3 moderate	20	5	9 (3 moderate)	6	−10 %	
13	21,5 easy/3 moderate	24,5	5	8	11,5 (3 moderate)	23 %	11 %
14	21,5 easy/3 moderate	24,5	5	11,5 (3 moderate)	8	0 %	
15	21,5 easy/3 moderate	24,5	5	8	11,5 (3 moderate)	0 %	
16	19 easy/3 moderate	22	5	10 (3 moderate)	7 inc. PPT	−10 %	

The content is displayed in relation to the four training variables: intensity, volume, frequency and progression and for each of the 16 weeks. The kilometers to be completed in each running session are outlined in the collums of session 1 – 3. All kilometers are run at an intensity equal to easy pace, except if moderate or hard is specified (easy pace ≈ 50–80%VO2max, moderate pace ≈ 81–87%VO2max and hard pace ≈ 88–100%VO2max). The volume outlined in the parenthesis will then be completed in the specified pace. The progression is in total weekly volume. PPTis the abbreviation used for Physical Performance test

**Fig. 2 Fig2:**
[figure not shown]
Development of the intervention during the entire follow-up. Volume (km/week) is the weekly total running volume. Intensity (km/week at moderate-hard pace) is the amount of kilometers at an intensity higher than 81 % VO2max. Schedule Intensity (blue) is focused on increasing the running intensity. Schedule Volume (grey) is focused on increasing the running volume

#### Preconditioning period

All included participants follow the same running schedule during the 8 week preconditioning period. The running frequency is 3 running sessions per week, the progression in running volume follows the outlined structure of the 4-week cycle and all running will be performed at an intensity equal to an easy or moderate pace.

#### Intervention training period

*Sch*-*I* (Intensity training group) is exposed to increased running volume at a hard pace (defined as an intensity equal to or above a VO2max of 88 %). The total running volume per week is fixed, and only kilometers at a hard running pace follow the progression in running. The running volume at a hard pace will increase in each 4 week progression cycle (Fig. 2). The remaining distance will be performed at an easy pace (defined as an intensity below a VO2max of 80 %).

*Sch*-*V* (Volume training group) is focused on increasing the total running volume per week. All scheduled running will be performed at either an easy or moderate pace (defined as an intensity equal to or below a VO2max of 88 %). Only the total running volume per week follows the progression in running (Fig. 2).

The intervention in both groups is presented in Fig. 2 and Tables 1, 2 and 3.

### Follow-up

Follow-up measurements collected are weight, OSTRC injury severity score [33], SQUASH questionnaire [28] and self-administered performance tests.

The OSTRC questionnaire is administered every Sunday on a weekly basis. If a participant has not answered the OSTRC questionnaire the following Monday, an automated reminder e-mail is forwarded, requesting an answer. At the end of the first 8 weeks of follow-up, the preconditioning period ends, and follow-up measurements are collected. These measurements are also used as baseline measurements for the following 16 weeks intervention training period (baseline 2). During the intervention training period, follow-up measurements are collected 2 times: after 8 weeks and at end of follow-up (Fig. 3).

**Fig. 3 Fig3:**
[figure not shown]
Follow-up measurements during the 24 weeks. The OSTRC questionnaire is administered every Sunday. Baseline 1, is the measurements collected at inclusion. Baseline 2, 8 weeks follow-up and End of follow-up is the follow-up measurements

### Randomization

The randomization procedure is applied through a random sequence allocation in the back-end system of the internet-based training diary. The algorithm applied ensures equal group size. Participants are allocated to schedule *Sch*-*I* or *Sch*-*V* at inclusion, using concealed even or odd numbers generated by the back-end system, which is only accessible by the investigators. The group allocation is also concealed to the investigator, until after inclusion of a participant, as the number allocation is based on, is generated after a participant is included. The diagnostic team assessing injuries (outcome) is blinded to group allocation when collecting data on outcome.

### Outcome

The primary outcome is injury defined as a Running-Related Injury (RRI): *An injury sustained on muscles, joints, tendons and/or bones during or after running and attributed to running. The injury must have caused a training reduction (reduced distance, intensity, frequency etc.) for at least 7 days* [19], [34].

The secondary outcome is symptoms of overuse injury defined as: *A physical problem perceived as pain, tenderness, stiffness, aching, looseness, locking or instability in any part of the body* [25]. The information is collected using a modified version of the OSTRC questionnaire [25]. The modification of the questionnaire consists of an addition to the possible answers in the fourth and last question *“Cannot participate due to pain”*. The included anatomical areas are: foot, ankle, front of lower leg, calf, knee, thigh, hamstrings, groin, glutes, hip and lower back. An approach similar to the one used by Clarsen et al. [33], is applied to ease the response load on the participants.

All participants who report an RRI are referred to injury diagnosis, performed by a physiotherapist. Injury diagnosis is carried out using a standardized examination protocol and standardized diagnostic criteria [10]. The OSTRC questionnaire will continue to be administered to participants who are diagnosed with an injury, in order to explore the severity of injuries.

### Power

The power calculation was based on a superiority calculation. Based on comparisons between the current and previous studies, considering differences between populations and interventions, and including experiences from clinical practice, an injury incidence of 20 % is expected in runners focusing on volume and an injury incidence of 35 % is expected in runners focusing on intensity [18, 19]. To be able to show a minimum difference in injury risk between groups of 5 %, a sample size of 620 participants is required to reach a power of 80 %. An accommodation to a potential loss to follow-up is necessary to include in determining the number of participants needed. In prospective studies with a self-structured running regime and a follow-up ≥ 6 months, the loss to follow-up have been reported to be approximately 22–30 % [34, 35]. Prospective studies with a structured running regime, and follow-up periods of 13 weeks, reported the loss to follow-up to be approximately 8 and a 60 % completion of the scheduled running [12, 19]. Taking into consideration the duration of the 24-week follow-up period in the present study, and the motivational factor possibly associated with a structured running regime, a potential loss to follow-up of 15 % is hypothesized, which leads to a required sample size of 713 participants.

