Training errors are recognized as a risk factor for running-related injuries and in order to develop running schedules with a minimized risk of injury, a better understanding of the different training variables’ influence on injury risk is needed [14, 15]. Trials investigating differences in injury risk in relation to the progression in running volume, the frequency and duration of running and participation in a preconditioning programme, have been conducted [16–18]. The GRONORUN 1 and 2 trials both mentions the application of an subjective measure of running intensity as a limitation in the trials [19, 20]. The study by Pollock et al.[18] used maximal oxygen uptake as a relative measure of running intensity, comparing different durations of running and different weekly running frequencies. However, the sample consisted of male prison inmates between 20 and 35 years of age, which makes it difficult to generalize the results to recreational or novice runners. A review by Nielsen et al. concluded that there are moderate evidence suggesting that volume is associated with injury risk, but that this association possibly is influenced by the weekly progression in volume and the maturation of the runners [15]. The existing literature on running intensity and the development of injuries show conflicting results, possibly related to the subjective measure used in previous studies [15]. A possible association between the focus of a running schedule and the risk of sustaining specific injuries has also been hypothesized. Specifically, patellofemoral pain, illiotibial band syndrome and patellar tendinopathy were hypothesized to be distance-related, while achilles tendinopathy, gastrocnemius injury and plantar fasciitis were hypothesized to be pace-related [21]. Findings from both experimental and cohort studies support this hypothesized association. In an experimental study by Petersen et al. [22], an increase in running speed resulted in an increase in the peak plantar flexion moment, which was significantly higher than the increase in the peak knee extensor moment (*p* < 0.05). In another experimental study by Petersen et al. [23], a decreased running speed resulted in a cumulative load at the knee joint which was significantly higher, compared with the cumulative knee joint load at higher running speeds [22, 23]. An observational study by Nielsen et al. [24], with a 1-year follow-up and 847 novice runners included, investigated the progression in volume and found that greater progression in running volume increased the risk of the above mentioned distance-related injuries, but not the overall risk of injury. The aim of the Run Clever trial is therefore to conduct a training schedule intervention trial, comparing a running schedule which focus on running intensity with a running schedule which focus on running volume, with the purpose of extending the above mentioned studies, by investigating the difference in risk between the two training variables and the risk of sustaining specific injuries associated with a specific training variable. The following hypotheses are tested (H).Runners with a focus on running intensity have a 15 % increased risk of injury compared with runners with a focus on running volume.A running schedule focusing on intensity, increase the risk of sustaining achilles tendinopathy, gastrocnemius injuries and plantar fasciitis compared with hypothesized distance-related injuries.A running schedule focusing on running volume, increase the risk of sustaining patellofemoral pain syndrome, illiotibial band syndrome and patellar tendinopathy compared vwith hypothesized pace-related injuries.A positive excess risk due to interaction exists between running intensity and running volume, and the effect is more pronounced for pace-related injuries with greater changes in speed than volume, while the effect is more pronounced for distance-related injuries with greater changes in volume than in speed.

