### Statistical analysis

All data will be analyzed using an instrumental variable approach in the primary analysis [36]. The instrumental variable is the randomization. Secondary analyzes are intention-to-treat and per-protocol. Time to first injury is analyzed using the following primary time scale: calender time in days and weeks. Data will be analyzed at the following time-points: 2 weeks, 4 weeks, 8 weeks and 16 weeks after randomization. Secondary time scales are cumulative running volume in kilometres and cumulative running volume in minutes. Time of follow-up begins when the randomized interventions start. The unit of analysis is each participant. Participants will be right-censored in case of pregnancy, disease, lack of motivation, non-running-related injury causing a permanent stop of running, unwillingness to attend clinical examination in case of injury, if more than 10 % of all training sessions were uploaded manually (they will be censored at the time 10 % of uploads are manual) or at end of follow-up, whichever comes first.

The injury proportion as a function of the follow-up time scales mentioned above will be estimated using the Kaplan-Meier curve. The cumulative injury risk difference between groups is analyzed, performing a generalized linear regression, using the pseudo values method [37]. Competing risk analysis will be performed separately for both groups, to investigate difference in risk of hypothesized injuries including more than one endpoint [38]. The Aalen Johansen estimator will be applied in the competing risks analysis. Endpoints included in the competing risk analysis are non-running-related injury causing a permanent stop of running and the 20 injuries presented by Taunton et al. [13] In the intensity group (Sch-I) the risk of achilles tendinopathy, gastrocnemius injuries, and plantar fasciitis are analyzed in a competing risk model, treating the remaining 17 injuries as competing events. In the volume group (Sch-V) the risk of patellofemoral pain syndrome, iliotibial band syndrome, and patellar tendinopathy are analyzed in a competing risk model, treating the remaining 17 injuries as competing events [21]. Differences are considered statistically significant at *p* < .05, and estimates are presented with 95 % confidence intervals. All analyzes are performed using STATA/SE version 13 (or more if applicable).

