The superiority power calculation based on a minimum risk difference between groups of 5 %, and taking a hypothesized loss to follow-up of 15 % into account, revealed a required sample size of 713 participants to reach a power of 80 %. A predetermined inclusion period of 6 months has been determined. The challenge of including 713 participants over a 6 month period is acknowledged. However, the estimated 31 % of the adult population in Denmark who participates in recreational running, provides an approximate background population of 904.685 persons, from which recruitment of participants can take place (Based on numbers from Statistics Denmark) [45]. Information regarding the possibility of participation in the trial is announced through the two largest Danish recreational running organizations. Possible participants can easily access and fill out the inclusion/exclusion questionnaire and indicate their interest in participation. The baseline information is collected through the online training diary, making data collection less time consuming for both participants and investigators. This gives us reason to assume that such a large scale inclusion is possible. However, a sample size of 357 participants, based on a minimum risk difference between groups of 1 %, with a power of 80 % and taking the hypothesized loss to follow-up of 15 % into account, is the minimal acceptable number of included participants and also the minimal acceptable clinical relevant difference. At the end of the 6 month inclusion period, no additional inclusions will be made.

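### 620 and 357 participants are said to show differences of 5 % and 1 %, but the figures fit 20 % v 35 % with unnamed superiority margins, and no margin rule is stated

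*Protocol article*

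**What the plan says.** - **Power section, type and inputs.** "The power calculation was based on a superiority calculation". The assumed risks are "an injury incidence of 20 % is expected in runners focusing on volume" and "an injury incidence of 35 % is expected in runners focusing on intensity", an expected gap of 15 percentage points.
- **Power section, result.** 620 participants are required for 80 % power "To be able to show a minimum difference in injury risk between groups of" 5 %. Allowing for 15 % loss gives 713.
- **Discussion, fallback.** The article accepts "a sample size of 357 participants, based on a minimum risk difference between groups of" 1 %, again at 80 % power and with the 15 % loss included. It adds that this "is the minimal acceptable number of included participants and also the minimal acceptable clinical relevant difference".
- **Statistical analysis.** The cumulative injury risk difference is analysed by regression on pseudo-values, with an instrumental-variable approach as primary. "Differences are considered statistically significant at" the .05 level, and 95 % confidence intervals are given. No null value other than the default, no margin and no confidence-limit rule is stated.
- **Background, first hypothesis.** The intensity group is expected to have a 15 % "increased risk of injury compared with runners with a focus on running volume".

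**The concern.** At the same power and loss allowance, the smaller difference (1 %) is paired with half the sample of the larger one (5 %). For detectable differences the order must be the reverse. So 5 % and 1 % are not differences that these samples can show with 80 % power, although the text says so.

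The stated power therefore does not belong to the analysis described. A reader of a null result could take it that 5 points, or even 1 point, had been looked for with 80 % power. In addition, the difference on which the design rests changes with the number of runners recruited, and the fallback value of 1 % is the one labelled clinically relevant.

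**Working it through.** **Inputs.** Risks pV = 0.20 and pI = 0.35, power 80 %, totals 620, 713 and 357, and loss 15 % (Power and Discussion). Equal groups (Randomization). Level 0.05 (Statistical analysis), taken as two-sided: this is my assumption, as sidedness is not stated. (1.960 + 0.842)² = 7.849. Unpooled variance: 0.20 × 0.80 + 0.35 × 0.65 = 0.3875.

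**1. Reproducing the plan's figures with a margin m.** n per arm = 0.3875 × 7.849 / (0.15 − m)².

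| Margin | Unpooled, per arm | Total | Other variance forms, total | Plan, before loss |
|---|---|---|---|---|
| 5 points | 3.0414 / 0.10² = 304.1 | 610 | 622 (null variance pooled), 626 (pooled throughout) | 620 |
| 1 point | 3.0414 / 0.14² = 155.2 | 310.4 (312 if rounded up per arm) | 318, 320 | about 310 |

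The loss allowance is a multiplication by 1.15: 620 × 1.15 = 713 and 310 × 1.15 = 356.5, rounded to 357. A one-sided 5 % level gives only 480 to 494 for the 5-point margin (520 with continuity correction), so it does not reproduce 620.

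**2. Other readings of the same figures.**
- 20 v 35 % against zero needs 276 in total (302 with continuity correction). That does not explain 620. Inflated for loss, 302 becomes 348 (× 1.15) or 356 (÷ 0.85), so 357 alone lies close to this reading, but the reading makes no use of the stated 1 %.
- A true difference of 5 points needs 2,188 in total at 20 v 25 %. A true difference of 1 point needs 51,166 at 20 v 21 %.

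**3. Power for the differences as worded.** With p̄ the mean of the two risks p1 and p2, and d their difference:

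power = Φ{ [ d√n − 1.96 √(2p̄(1 − p̄)) ] / √(p1(1 − p1) + p2(1 − p2)) }

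| True risks | Analysed | Power |
|---|---|---|
| 20 v 25 % | 620 | 31.9 % |
| 30 v 35 % | 620 | 26.4 % |
| 20 v 21 % | 310 | 4.1 % |
| 34 v 35 % | 310 | 3.8 % |
| 20 v 35 % | 620 | 98.8 % |
| 20 v 35 % | 310 | 84.4 % |

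The power counts rejections in the expected direction only. Solving the same formula for 80 % power from a 20 % base gives a detectable difference of 9.7 points with 620 and 14.1 points with 310.

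**4. Power if a margin is tested.** Power = Φ[ (0.15 − m) / √(0.3875/n) − 1.96 ].
- 310 per arm, 5 points: 0.10 / 0.03536 = 2.828, power 80.7 %.
- 155 per arm, 1 point: 0.14 / 0.05 = 2.80, power 80.0 %.
- 155 per arm, 5 points: 0.10 / 0.05 = 2.00, power 51.6 %.

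So the fallback size keeps 80 % power only because the margin drops from 5 points to 1.

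**5. Sensitivity to adherence.** The Power section cites 60 % completion of scheduled running in earlier structured programmes. Suppose that 20 % and 35 % are risks under full adherence and that the difference as assigned shrinks in proportion (my assumption). At 80 % adherence the contrast is 20 v 32 %, and the formula in step 3 gives 93 % at 620 and 67 % at 310. At 60 % it is 20 v 29 %, giving 74 % and 45 %.

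**The case against.** **The arithmetic is not wrong.** The article announces a superiority calculation, gives both expected risks and then a minimum difference. Those are the inputs of a margin calculation, and 620 and 357 come out of it. This stands. The totals of 2,188 and 51,166 describe the wording, not the calculation that was run. The fault is that the wording, the calculation and the described analysis do not match.

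**A reader might infer that no margin test will ever be done, or that the analysis is explicitly a test against zero.** The article does not support either. It names no null value, a 95 % interval for the risk difference could be compared with a margin, and an analysis plan that is not shown may hold the rule. What can be said is that the article states none.

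**A reader might infer that both figures can arise only from margins.** That is firm for 620 among the readings tried. For 357 it is not strict, as step 2 shows.

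**A reader might infer that clinical relevance itself is moved from 5 % to 1 %.** Only the 1 % carries that label, and the passage can be read as a preferred target plus a pre-stated floor. What survives is that the design difference is tied to recruitment.

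**A reader might take the 15 % in the first hypothesis as relative.** The stated risks already settle it as percentage points, so this is a matter of wording only.

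**A reader might conclude that the trial is too small.** For the expected 20 v 35 % against zero it is not, on the simple calculation. Nor does the article say that a null result will be taken to exclude 5 or 1 points. That risk lies in how readers would use the stated power.

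**Conclusion.** The point holds as a mismatch between the stated power and the analysis described. Read literally, 80 % power for 5 % and 1 % is in fact about 32 % (26 to 32 % across the base risks tried) at 620 and about 4 % at 310. The figures are explained by 5- and 1-point superiority margins around 20 v 35 %, which the article neither names nor attaches to a decision rule. The difference behind the design then changes with recruitment.

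This rests on equal arms, a two-sided 5 % level and a plain comparison of two proportions with complete data. The 99 % and 84 % for 20 v 35 % against zero hold only if those are the risks as assigned. Non-adherence, censoring and the instrumental-variable analysis would lower them, and the article does not say which kind of risk is meant.

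**What to change.** Delete the statements that 620 and 357 participants show differences of 5 % and 1 %, and choose one of two options.

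- **(a) Test against zero.** Say so, and state that for a simple two-proportion comparison with complete data and as-assigned risks of 20 % and 35 %, power is about 99 % at 620 and 84 % at 310, with 80 % power for about 9.7 and 14 points from a 20 % base. Label these figures as conditional, and say that non-adherence, censoring and the instrumental-variable analysis would lower them.
- **(b) Test against a margin.** Name one superiority margin, fixed whatever the recruitment, and require the lower 95 % confidence limit of the risk difference to exceed it. If the margin is 5 points, say that 310 analysed give only about 52 % power.

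Under either option, state one minimal relevant difference that does not depend on recruitment, and word the first hypothesis as 15 percentage points.

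The cost is rewording of the Power section, one Discussion paragraph and the first hypothesis, plus one sentence in Statistical analysis for the chosen null value or rule. No extra participants are needed. The stated detectable difference under (a), or the power at the fallback size under (b) with a 5-point margin, becomes less favourable.
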